### *Economic analyses*

Quality-adjusted life-years (QALYs) will be obtained from the SF-6D (22). Cost evaluation will be conducted to record the costs of implementation in the community setting from the perspectives of health service providers. Incremental costs and incremental effects will be compared between the self-acupressure and KHE groups. The incremental cost-effectiveness ratio (ICER) will be calculated by:  $\Delta \text{ costs} / \Delta \text{ effects}$ , where  $\Delta \text{ costs}$  represents the difference in the costs between self-acupressure and KHE groups, and  $\Delta \text{ effects}$  represents the difference in the QALYs (changes in SF-6D scores) between the two groups.

To test the robustness of the ICER and quantify the uncertainty in these ratios, bootstrapping involving 5,000 iterations will be performed and the results will be

plotted in a cost-effectiveness plane. A cost-effectiveness acceptability curve displaying the probability that the intervention is cost effective for a range of willingness-to-pay ceilings will also be estimated by using the bootstrapped ICERs in probabilistic sensitivity analysis. To confirm the robustness of the base-case findings, scenario analysis will be conducted by testing several assumptions made in the base-case scenario. Impacts of these assumptions on the ICER will be assessed.

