#### Rationale of the control group

Since acupressure training involves much contact time between the instructor and participants, the improvement in participants' pain, if any, may be attributed to non-specific effects from the subject-practitioner interaction. Care as usual and waitlist control used in previous studies are not able to control for such non-specific effects and even lead to placebo effects due to "not being treated". Therefore, in this proposed study, knee health education for the same length as in the self-administered acupressure group is adopted to control the contact hours between the instructor and participants. If our self-administered acupressure training is found to be more effective than education, then it can be examined in further studies to compare with other standard interventions or exercise programs.

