### Assessment of costs

Cost evaluation will be conducted to record the additional costs of implementing the self-acupressure training course for knee OA in the community centre setting from the perspectives of health service providers. Total costs will be summation of interventional costs, direct medical costs and direct non-medical costs.

Interventional costs will be included such as staff costs for organizing the course and running the course, telephone follow-up after the course, teaching materials, consumable materials, and rental cost of venue. To estimate the time cost of staff for organizing and preparing the course, the time spent on the program by each staff member (instructor, course assistant, and research assistant) will be recorded for

each course. The average number of minutes spent will be multiplied by the relevant salary rate per minute. The cost of teaching materials including the handouts, and other consumable will also be calculated. Besides, direct medical costs will account for the number of healthcare service visits during the trial period, whereas the direct non-medical costs will estimate transportation costs related to intervention and course attendance.

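### The acceptability curve is to be built from bootstrapped ICERs, which cannot be ranked across quadrants; it should use net monetary benefit, and transport costs need to match the stated provider perspective

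*Protocol*

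**What the plan says.** The Economic analyses section of the protocol defines the ICER as delta costs divided by delta effects. The numerator is the between-group cost difference; the denominator "represents the difference in the QALYs (changes in SF-6D scores) between the two groups". For uncertainty, the plan is a bootstrap of 5,000 replicates, with its output "plotted in a cost-effectiveness plane". The acceptability curve, drawn across willingness-to-pay thresholds, "will also be estimated by using the bootstrapped ICERs in probabilistic sensitivity analysis". The section mentions neither net monetary benefit nor a rule for negative ratios or for the separate quadrants of the plane.

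Assessment of costs says that costs are taken "from the perspectives of health service providers", and Economic analyses repeats that perspective. Assessment of costs also makes total cost the sum of intervention, direct medical and direct non-medical costs, where "direct non-medical costs will estimate transportation costs related to intervention and course attendance".

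**The concern.** An acceptability curve needs a yes or no for each replicate at each ceiling: is acupressure worth its extra cost compared with knee health education? The ICER answers that only when the QALY difference is positive. When it is negative, the inequality reverses. A dominated replicate (dearer and worse) has a negative ratio and so falls below any positive ceiling, exactly as a dominant one does. In the south-west quadrant (cheaper and worse) a low ratio means little money saved per QALY given up, which is unfavourable, yet it too falls below the ceiling.

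The probability of cost-effectiveness is the figure a funder would read from this analysis. Small QALY differences are plausible here: follow-up is 12 weeks, the comparator is an active education course, and the trial is sized on NRS pain, not on the SF-6D. A curve that stays high when there is no QALY gain would mislead in just that case.

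The transport item is a separate inconsistency in what goes into delta costs.

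**Working it through.** **Plan's own figure.** The economic section states no cost, QALY or ceiling value, so there is nothing to reproduce. All values below are assumptions.

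**Inputs.** Q = bootstrapped QALY difference, normal, standard error 0.003. C = bootstrapped cost difference, normal, standard error 60, independent of Q. Ceiling L = 50,000 per QALY. The means are varied.

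**Two counting rules.**
- Ratio rule: count the replicate if C/Q < L.
- Net-benefit rule: count it if NB = L × Q − C > 0.

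For Q > 0 they agree. For Q < 0, multiplying C/Q < L by Q reverses the sign, so the ratio rule counts exactly the replicates with NB < 0. Hence

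overstatement = P(Q < 0 and NB < 0) − P(Q < 0 and NB > 0),

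which can never exceed P(Q < 0).

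**Spread of NB.** L × SE(Q) = 50,000 × 0.003 = 150. SE(NB) = √(150² + 60²) = √26,100 = 161.6. Correlation of Q with NB = 150/161.6 = 0.928.

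**No effect on either.** P(NB > 0) = 0.500. The ratio rule counts replicates in which Q and NB have the same sign: 1 − arccos(0.928)/π = 0.879.

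**One standard error of QALY gain (0.003), equal costs.** P(NB > 0) = Φ(150/161.6) = Φ(0.928) = 0.823. P(Q < 0) = Φ(−1) = 0.159, which splits into 0.129 wrongly counted and 0.030 wrongly dropped. Ratio rule: 0.823 + 0.129 − 0.030 = 0.923 with unrounded terms.

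**Range**, from the bivariate normal distribution:

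| Mean Q | Mean C | P(Q < 0) | Ratio rule | Net benefit | Overstatement |
|---|---|---|---|---|---|
| 0 | 0 | 0.500 | 0.879 | 0.500 | 0.379 |
| 0.001 | 50 | 0.369 | 0.838 | 0.500 | 0.338 |
| 0.003 (1 SE) | 0 | 0.159 | 0.923 | 0.823 | 0.100 |
| 0.003 (1 SE) | 50 | 0.159 | 0.873 | 0.732 | 0.141 |
| 0.003 (1 SE) | 150 | 0.159 | 0.658 | 0.500 | 0.158 |
| 0.006 (2 SE) | 0 | 0.023 | 0.980 | 0.968 | 0.012 |
| 0.006 (2 SE) | 150 | 0.023 | 0.846 | 0.823 | 0.023 |
| 0.009 (3 SE) | 0 | 0.001 | 0.998 | 0.997 | 0.001 |

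**Second set of assumptions**, simulated with the protocol's 133 per group, individual QALY SD 0.02, cost SD 100 and ceiling 20,000. The standard errors are 0.02 × √(2/133) = 0.00245 and 100 × √(2/133) = 12.3. With equal costs, ratio rule against net benefit: 0.922 against 0.501 at no QALY gain, 0.943 against 0.787 at a gain of 0.002, and 0.989 against 0.976 at 0.005.

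**What drives the error.** It follows P(Q < 0), so it depends on the QALY difference relative to its standard error. At a mean gain of 0.003, moving the mean cost difference from 150 to 0 lowers the dominated share from 0.158 to 0.079 and the overstatement from 0.158 to 0.100.

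**Transport.** Set side by side, Assessment of costs adopts the provider's perspective and then counts travel related to the intervention and course attendance in the total. Nothing in the protocol says that the provider pays for that travel. Without such a statement, the perspective and the list of cost items do not match.

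**The case against.** The strongest reply is that the protocol states no counting rule. The replicates are plotted in the plane, so the pairs of cost and QALY differences exist, and the reference to bootstrapped ICERs may be shorthand for those pairs. A statistical analysis plan, not shown here, may settle it. This stands as far as it goes: a reader might infer that dominated replicates will be counted as cost-effective, and the text does not say so. But the protocol does more than stay silent. It assigns the replicates to the plane and the ratios to the curve, so an analyst who follows it literally works from the wrong quantity.

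A second reply is that the size is entirely assumed and fades once the QALY gain is clear. That is correct, and the table shows it.

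A reader might also infer that the equal-length control course ("knee health education for the same length as in the self-administered acupressure group is adopted to control the contact hours") pushes the cost difference toward zero and so causes the problem. The documents do not support this. Matched contact hours limit the difference in course cost, but healthcare visits and travel also count, the instructors come from different professions, and no section predicts a near-zero difference. The mechanism also runs the other way, as the calculation shows.

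On transport, the protocol does not name the payer, and travel to equally many sessions may largely cancel between groups. The effect on the ICER may therefore be small, but the mismatch with the stated perspective remains.

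**Conclusion.** The point holds as a defect in the named method, conditional on the text being applied literally. The ratio rule then inverts the decision for every replicate with a negative QALY difference. Under the stated assumptions (normal, independent differences; QALY standard error 0.003; cost standard error 60; ceiling 50,000) it gives about 88% instead of 50% with no effect on either, 92% instead of 82% at one standard error of QALY gain with equal costs, and 1 to 2 points too much at two standard errors. The upward direction was shown for mean cost differences of zero or more. If acupressure were much cheaper, the replicates wrongly dropped could outnumber those wrongly counted.

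The mismatch between the provider perspective and the transport item is real but separate, and its size cannot be judged from the protocol.

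A reader might go further and say that netting off the control course hides the cost of implementation. That does not follow: the protocol records staff time, materials and venue directly, and subtracting the comparator's cost is what an incremental analysis does.

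This is a secondary economic analysis. The primary outcome and the sample size are unaffected.

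**What to change.** Change the sentence on the acceptability curve to say that, for each bootstrap replicate, net monetary benefit = ceiling × delta QALY − delta cost is computed, and that the curve shows the share of replicates above zero at each ceiling. Keep the plane, and report the ICER only as a point estimate beside it.

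For costs, either take transport out of the provider-perspective total and show it in one of the scenario analyses already planned, or restate the perspective so that it covers travel.

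Both changes use data already being collected and need a few lines of code. The price is that the reported probability of cost-effectiveness will probably be less favourable if the QALY gain is small.

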## **6. Purpose and Potential**

The findings of this project will be critical in determining the clinical effectiveness of offering a short acupressure training course to teach middle-aged and older to perform self-administered acupressure to relieve their knee pain. Knee OA is a prevalent condition leading to many negative health consequences, and it is expected to be more prevalent due to the aging population.

Self-administered acupressure is less time-consuming and at minimal cost. If found to be effective, we can recommend self-administered acupressure as an evidence-based strategy to healthcare providers for relieving knee OA pain in the community. Effective self-administered acupressure treatments could be made available to people knee OA in the community as an adjunct intervention to their current pain therapy and probably reducing their consumption of painkillers and prevent deterioration of their condition. The self-administered acupressure can be taught by Chinese medicine practitioners and other healthcare professionals such as nurses or physiotherapists. This cost-effective method will significantly relieve the burden on the public healthcare system. Healthcare providers, public health policy-makers, and individuals with knee OA will greatly benefit from the findings of this study.

## **7. Ethical approval**

The protocol will be submitted to the Hong Kong Polytechnic University institutional review board and Institutional Review Board of the University of Hong Kong/ Hospital Authority Hong Kong West Cluster for approval. The study will be conducted according to the "Declaration of Helsinki". Participation in the study is voluntary. An information sheet is provided and a written consent is required from the participant.

## **8. Potential hazards to participants**

Since both self-administered acupressure and knee health education are non-invasive, the problem of adverse event will be minimal. The treatments used in the protocol have been tested in the pilot study and no participant had reported significant side effects. It is likely that the subjects experience slight discomfort when they are requested to apply pressure on the acupoints. Such a phenomenon will be explained

to the subjects in advance and the pressure will only be applied for a short period of time, which would obviously not produce any injury to the subjects. We will have phone calls and Whatsapp reminders (twice per week) and the subjects can raise questions if they have encountered any discomfort. The subjects can also call our Research Assistant at any time to have our assistance.

**Table 1. Assessment Schedule**

|                                                                 | Screening | Baseline | Training period
(2 weeks) |   | Assessment
time points |   |    |
|-----------------------------------------------------------------|-----------|----------|------------------------------|---|---------------------------|---|----|
| Week of study                                                   | -1        | /        | 1                            | 2 | 4                         | 8 | 12 |
|                                                                 |           |          |                              |   |                           |   |    |
| Review inclusion/exclusion criteria                             | √         | √        |                              |   |                           |   |    |
| Demographics                                                    | √         |          |                              |   |                           |   |    |
| Medical History                                                 | √         |          |                              |   |                           |   |    |
| Height & Weight                                                 | √         |          |                              |   |                           |   |    |
| Vital signs                                                     | √         | √        | √                            | √ | √                         | √ | √  |
| Primary Outcome                                          |           |          |                              |   |                           |   |    |
| Pain Severity Numerical Rating Scale                            | √         | √        |                              |   | √                         | √ | √  |
| Secondary Outcomes                                       |           |          |                              |   |                           |   |    |
| Western Ontario and McMaster
University Osteoarthritis Index |           | √        |                              |   | √                         | √ | √  |
| Short Form-Six Dimensions                                       |           | √        |                              |   | √                         | √ | √  |
| Timed Up & Go Test                                              |           | √        |                              |   | √                         | √ | √  |
| Fast Gait Speed                                                 |           | √        |                              |   | √                         | √ | √  |
| Medication Use                                                  |           | √        |                              |   | √                         | √ | √  |
| Others                                                   |           |          |                              |   |                           |   |    |
| Acupressure/ health instruction logbook                         |           |          | √                            | √ | √                         | √ | √  |
| Adverse event monitoring                                        |           |          | √                            | √ | √                         | √ | √  |
